# Effects of novel diabetic therapeutic footwear on preventing ulcer recurrence in patients with a history of diabetic foot ulceration: study protocol for an open-label, randomized, controlled trial

**DOI:** 10.1186/s13063-021-05098-8

**Published:** 2021-02-17

**Keywords:** Diabetic therapeutic footwear, Ulcer recurrence, Diabetic foot ulcers, Randomized controlled trial, Adherence to treatment

## Abstract

**Background:**

Recurrence after the healing of a foot ulcer is very common among patients with diabetes mellitus. Novel diabetic therapeutic footwear consisted of merino wool, vibration chip, and orthopedic insoles is designed to influence multifaceted mechanisms of foot ulcer occurrence. The aim of this study is to examine the effect of the optimally designed therapeutic footwear on preventing ulcer recurrence in patients with a history of diabetic foot ulcers (DFU).

**Methods/design:**

The trial is designed as a two arms, parallel-group, open-label randomized controlled intervention study. The Log-rank Test was used for calculating sample size based on the latest national multicenter survey data of DFU in China. Three hundred and twenty participants will be recruited from the Diabetic Foot Care Center, West China Hospital, Sichuan University. Adults with diabetic peripheral neuropathy, healed foot ulceration in the 3 months prior to randomization, and aged ≥18 years, will be recruited. Participants will be randomized to receive novel diabetic therapeutic footwear (*n* = 160) or their own footwear (*n* = 160). The primary outcome will be the incidence of ulcer recurrence. The secondary outcome will be measurements of barefoot dynamic plantar pressures, the influence of footwear adherence on ulcer recurrence, and the incidence of cardiovascular events. Assessment visits and data collection will be obtained at baseline, 1, 3, 6, 9, and 12 months. The intention-to-treat principle will be applied. A cox regression model will be used to calculate the hazard ratio for the incidence of ulcer recurrence. The change of barefoot dynamic plantar pressures will be assessed using repeated measures ANOVA. The study protocol has been approved by the Ethics Committee of The Biomedical Research Ethics Committee of West China Hospital, Sichuan University (Reference No. 2019(96)).

**Discussion:**

This clinical trial will give information on the ability of novel diabetic footwear on preventing ulcer recurrence in patients with a history of diabetic foot ulceration. If the optimally designed therapeutic footwear does work well, the findings will contribute to the development of innovative treatment devices for preventing foot ulcer recurrence in high-risk patients.

**Trial registration:**

Chinese Clinical Trial Registry ChiCTR1900025538. Registered on 31 August 2019.

**Supplementary Information:**

The online version contains supplementary material available at 10.1186/s13063-021-05098-8.

## Background

The development of foot ulcers is a significant marker of the extent of long-term complications in patients with diabetes mellitus, which is the most common reason for lower limb amputation [1]. Diabetes-related foot ulcers precede at least 60% of all nontraumatic lower limb amputations [2]. Mortality following amputation ranges from 50 to 68% at 5 years and is worse than that of many forms of cancer [2, 3]. Moreover, even after the resolution of a foot ulcer, recurrence is also common [4, 5]. A recent large cohort study in China showed that the incidence rate for foot ulcer recurrence within 1 year also reached 31.6% [5]. Therefore, prevention of ulcer recurrence or occurrence is of prime importance in the current approach to diabetic foot disease.

DFU is an outcome of a combination of multiple causes including pathophysiologic changes, foot deformities, and trauma [2]. Although pathophysiologic changes such as peripheral neuropathy or/and peripheral arterial disease (PAD) play a central role in the development of foot ulcers, foot deformities contributes directly to foot ulcer occurrence. These deformities as a result of diabetic autonomic and motor neuropathies lead to areas of increased peak plantar pressures, which are common sites of ulceration formation [2]. To reduce ulceration formation, diabetic therapeutic footwear for high-risk patients was widely recommended in clinical practice [6]. Reductions of plantar pressures, shear forces, and friction on the sole of the foot and the toes are primary mechanisms of therapeutic footwear, which are responsible for protecting against foot ulcers [6–16]. Data from observational studies suggested a significant protective benefit from improved custom-made footwear [7–12]. However, in well-designed randomized controlled trails (RCTs), no statistically significant benefit was observed in patients wearing improved footwear compared with those with usual care [13–15]. Based on several published reviews of clinical trials, the discrepancy between observational studies and RCTs might be attributed to characteristics of intervention shoes, adherence to treatment, risk factors for reulceration, and so on [15, 16]. Thus, footwear effectiveness may not only need a function of offloading but also adequate patients’ adherence [14–16].

For better patients’ adherence and multifactorial intervention aimed at multiple risk factors for DFU, novel diabetic therapeutic footwear consisted of merino wool, vibration chip, orthopedic insoles, and non-slip outsoles is recently designed for use by patients with diabetes (Fig. 1). Merino wool is a high-quality type of wool which enables the production of lighter and softer wool fabrics with its long and fine fibers [17]. Shoe vamp and lining with merino wool had unique water absorption capacity, could adjust the temperature of the sole of the foot and produce a feeling of coolness or warmth, resisted odor and pathogenic bacteria, and was not easy to cause itchy skin, which could improve comfort and patients’ footwear adherence [18–20]. Among patients with diabetes, microvascular and macrovacular disease frequently contribute to reduced blood perfusion and skin oxygenation of feet which were independently related to foot ulcer risk. Therefore, the intervention to improve foot circulation may be beneficial to lower foot ulcer risk. Vibration chip was developed as a whole body vibration (WBV) exercise device. Prior studies have showed that WBV was beneficial to increase lower extremity skin blood flow and muscle force. Moreover, it also could improve the sensation of plantar surface pressure and standing balance [21–24]. In addition, whole body vibration intervention also could improve glycemic profile and lipid-related cardiovascular risk factors [25]. Additionally, previous literature has documented that the forefoot (e.g., metatarsal heads and toes) and heel with increased peak plantar pressures were most common sites of DFU [26]. To relieve the pressure on the forefoot and heel, orthopedic insoles will be designed to provide more support for medial longitudinal and lateral arch and partly transfer pressure away from the forefoot and heel. Moreover, they will employ soft and skin-friendly design to reduce the risk of friction-related skin breakdown. Therefore, in view of the above mentioned mechanisms, we speculate that the novel diabetic therapeutic footwear may exert beneficial effect on preventing foot ulcers in patients with diabetes. We will conduct a randomized controlled trial to examine the effect of the novel diabetic footwear with vibration chip and merino wool on preventing ulcer recurrence in patients with a history of DFU. Secondly, we further assess the influence of patients’ footwear adherence on the efficacy of the diabetic footwear.

**Fig. 1 Fig1:**
[figure not shown]
Key components of optimally designed therapeutic footwear

## Objectives

The objectives of this trial are as follows:
To verify the efficacy of the therapeutic footwear with vibration chip and merino wool prevent ulcer in preventing ulcer recurrence among patients with a history of DFU.To determine whether the therapeutic footwear can reduce the plantar pressure among patients with a history of DFU.To examine whether patients wearing the therapeutic footwear have better feeling of comfort and higher footwear adherence and also assess the influence of patients’ footwear adherence on the efficacy of the therapeutic footwear.To examine whether patients wearing the diabetic footwear have fewer cardiovascular events than those wearing non-improved footwear.

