#### Follow-up visits

Participants will be followed at 1 month (visit 2), 3 months (visit 3), 6 months (visit 4), 9 months (visit 5), and 12 months (visit 6) after randomization. At each visit, the trial team will collect the information including incidence of foot ulcer, footwear adherence, cardiovascular events, glucose profile, and other cardiovascular risk factors control. For physical activity evaluation, participants will be asked to wear a pedometer (P084, SPORTWAY, ShenZhen, China) every day to record the date and steps taken per day. Meanwhile, a concealed activity monitor (Lifecorder Plus, Suzuken) will be attached to the diabetic therapeutic footwear. Activity data will be uploaded by a research assistant to a centralized server via internet at each follow-up visit. Adherence to treatment will be evaluated through the comparison of the step counts recorded by a concealed activity monitor with those recorded by a pedometer. Adherence to treatment will be monitored until the end of follow-up. Plantar pressure distribution patterns will be measured after randomization every 3 months. At the end of follow-up, ABI and blood flow parameters of lower extremities will also be collected. At each visit, if participants make a withdrawal request or are not eligible to continue due to the presence of severe concomitant diseases or conditions listed in the exclusion criteria, they will be discontinued from the study. For participants who drop out, the information including incidence of foot ulcer, footwear adherence, cardiovascular events, ABI (if possible), plantar pressures (if possible), and biochemical parameters (if possible) will be collected.

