#### Secondary outcome measures

The secondary outcome measures include (1) the change of barefoot dynamic plantar pressures, from the third to the sixth diaries compared with that from the first diary (screening period); (2) the influence of footwear adherence on ulcer recurrence; and (3) the incidence of cardiovascular events.

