### Statistical analysis

At the end of this trial, all original data without participants’ name and the random sequences will be sent to a statistician for data analysis. Statistical analysis will be performed using SAS version 9.4 (SAS Institute Inc., Cary, NC, USA). Significance level will be set at *α* = 0.05. Quantitative variables expressed as means ± standard deviation or median with interquartile range, and categorical data will be recorded as numbers and percentages. Between-group differences of continuous variables will be tested for significance using Student *t* test when original data or data via transformation of variables is normally distributed or using Wilcoxon rank-sum test when data is not normally distributed. A chi-square test will be used for categorical data.

The primary end point, ulcer recurrence, will be analyzed according to the intention-to-treat principle, with event curves for the time to the first event on the basis of Kaplan–Meier analysis, and treatments will be compared by means of the log-rank test. A cox regression model will be used to calculate the hazard ratio for the primary end point. Among secondary end points, plantar pressures at baseline and at 3, 6, 9, and 12 months will be compared with repeated measures ANOVA. The changes blood flow parameters of lower extremity at baseline and at 12 months will be compared using Student *t* test when these means between groups are comparable at baseline or using analysis of covariance (ANCOVA) when these means are not equivalent at baseline. For cardiovascular events, the hazard ratio for the comparison of treatment group with control group and 95% confidence intervals will be estimated with the use of a proportional-hazards model.

The footwear adherence will be calculated for each group and then ulcer recurrence rates will be compared between the subgroups of patients with high adherence and low adherence by *χ*^2^ tests. We also plan to explore whether potentially important covariates such as age, sex, body mass index, physical activity, and diabetic duration could potentially confound the results.

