In addition, adherence to treatment has been considered as an important factor to influence those clinical outcomes of RCTs [14, 15]. Patients who were adherent had significantly better outcomes than those who were nonadherent [14, 15]. Thus, we will ensure patients fully understand the importance of adherence to treatment through continuous education and meanwhile repeatedly urge patients to persist footwear adherence during the process of trial. Moreover, we also focus on identifying patients who are nonadherent or are anticipated to be nonadherent. After this trial is completed, the effect of footwear adherence on the outcomes on ulcer recurrence will be evaluated and then whether new technologies influence footwear adherence will also be assessed.

The main limitation of the study is the open-labeled design and single-institutional study. The patients’ preference and expectations from trial participation with a specific footwear therapy may lead to bias. However, due to the obviously different structures between therapeutic footwear and control footwear, it is difficult to blind participants to their allocated group. Participants will not be informed which footwear is under investigation for its capacity to protect against ulcer recurrence. I will also conceal participants’ allocation to outcome assessors and a statistician in order to try to minimize bias. Additionally, we are not able to purchase a reliable in-shoe pressure measurement system within China. Although the change of in-shoe plantar pressures is important, the measurement of in-shoe pressures is unavailable for us to examine the efficacy of the therapeutic footwear. Even so, the lack of in-shoe pressure measurement should have limited impact on assessing the effect of therapeutic footwear because ulcer recurrence is the primary outcome in the present trial.

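### Objective 3 asks how adherence changes the shoe's efficacy, but the one test fixed for it compares high with low adherers, without randomised controls, and cannot separate a shoe effect from patient selection

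*Protocol article*

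**What the plan says.** The article puts the adherence question in two ways. The Background (closing sentence) and the third item under Objectives ask about the influence of "footwear adherence on the efficacy of the therapeutic footwear". The Secondary outcome measures section lists "the influence of footwear adherence on ulcer recurrence", and the Abstract uses the same framing.

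The Statistical analysis section gives one method. It says "The footwear adherence will be calculated for each group", and then that "ulcer recurrence rates will be compared between the subgroups of patients with high adherence and low adherence", by chi-square test. The next sentence begins "We also plan to explore whether potentially important covariates such as age, sex, body mass index, physical activity, and diabetic duration" and concerns whether these could confound the results. It does not refer to the adherence test in particular.

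Under Follow-up visits, adherence is the step count from a concealed monitor set against the step count from a pedometer. The concealed monitor "will be attached to the diabetic therapeutic footwear"; none is described for control footwear. The same section states: "Adherence to treatment will be monitored until the end of follow-up".

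The Discussion says of earlier randomised trials: "Patients who were adherent had significantly better outcomes than those who were nonadherent".

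**The concern.** In this trial, efficacy means a difference from the own-footwear arm. A question about how adherence changes efficacy therefore needs that arm in the comparison, and the planned test leaves it out. The patient decides after allocation how much to wear the shoe. Patients who wear it diligently may also inspect their feet, control their glucose and walk differently. A lower recurrence rate among them could come from the shoe, from those habits, or from both. Measuring adherence more accurately would not resolve this.

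What is at stake is interpretation. The Background reports that well-designed randomised trials of improved footwear found no significant benefit and lists adherence among the possible reasons. If the intention-to-treat result here is also null, a significant high/low difference could easily be read as showing that the shoe works when worn. The planned test could produce that difference with an ineffective shoe.

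**Working it through.** **Question and method side by side.**

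- Background and Objectives: influence of adherence on efficacy. This needs treated versus control, by adherence.
- Secondary outcome measures: influence of adherence on recurrence. This is an association.
- Statistical analysis: high versus low adherers, chi-square. This matches the outcome wording but not the objective.
- Whether the subgroups are formed within the footwear arm or pooled across arms is not clear. Pooling would still not compare adherers with their randomised controls, and no control-arm monitor is described.

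The article gives no figure for the adherence test, so there is none to reproduce. Two illustrations show how far selection alone can move the result. Both assume that the shoe does nothing.

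**Illustration 1, closed form.**

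Inputs: 160 in the footwear arm and 31.6% one-year recurrence (Sample size calculation); a 50:50 split, so 80 versus 80 (assumption); a ratio RR of underlying risk, low to high adherers (assumption).

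The subgroup rates are p_high = 2 × 0.316 / (1 + RR) and p_low = RR × p_high.

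The chance of a significant result is Φ[(p_low − p_high − 1.96·SE0) / SE1], where SE0 = √(2 × 0.316 × 0.684 / n) and SE1 = √{[p_high(1 − p_high) + p_low(1 − p_low)] / n}.

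For RR = 1.5 and n = 80:

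- p_high = 0.632 / 2.5 = 0.2528 and p_low = 0.3792, a difference of 0.1264.
- SE0 = 0.0735 and SE1 = 0.0728.
- (0.1264 − 0.1441) / 0.0728 = −0.243, and Φ(−0.243) = 0.40.

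| RR | High | Low | 80 v 80 | 64 v 64 (after 20% loss) |
|---|---|---|---|---|
| 1.25 | 28.1% | 35.1% | 16% | 13% |
| 1.5 | 25.3% | 37.9% | 40% | 34% |
| 2.0 | 21.1% | 42.1% | 82% | 73% |

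Simulation at RR 1.5 and 2.0 gave 40% and 82% for the high/low test, against 4–5% for the comparison of randomised arms. At RR 1.0 both were about 5%.

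**Illustration 2, simulation.**

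Each patient has a latent log-risk, placed on the log-hazard scale, with standard deviation 0.7 and calibrated to 31.6% recurrence on average. It correlates with adherence by an assumed amount. The footwear arm is split at median adherence, with 160 per arm.

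- Correlation −0.1: the high/low test rejects in about 6–7% of trials.
- Correlation −0.3: recurrence is about 28% (high) versus 35% (low), and the test rejects in 19%.
- Correlation −0.5: about 25% versus 38%, and the test rejects in 43–44%.
- With the standard deviation varied from 0.5 to 1.0, rejection ranges from about 6% to about 65%.
- The randomised comparison rejects in 4–6% throughout.

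With 2,000 trials, the simulation error at 19% is √(0.19 × 0.81 / 2000) = 0.9 points. A positive correlation (higher-risk patients wearing the shoe more) would, by symmetry, bias the result the other way and could hide a real benefit.

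**What a complier estimate would and would not do.**

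Complier average effect = intention-to-treat risk difference / proportion adherent. With no shoe effect it averages about zero. It is the intention-to-treat difference rescaled, and it assumes that wear below the threshold does nothing.

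Suppose instead that wear is uniform on 0–1 and benefit is linear in wear (assumptions), with the planned difference of 77.9 − 64.8 = 13.1 points.

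- The estimate at threshold 0.5 is 13.1 / 0.5 = 26.2 points.
- Full-wear benefit is also 26.2, because mean wear is 0.5. Patients above 0.5 have mean wear 0.75, so their true benefit is 26.2 × 0.75 = 19.7 points.
- The estimate overstates that benefit by one third (26.2 / 19.65 = 1.33).

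**The case against.** The strongest reply is that the test does match the listed secondary outcome, which concerns recurrence and not efficacy. On that view only the wording of the Background and Objectives is loose. This stands, and it makes rewording the objective a legitimate remedy. It does not remove the need to say what an unadjusted high/low contrast can support.

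A second reply is that confounding is addressed by the planned covariate exploration. This stands in part, and it would be wrong to say that confounders are ignored. But the sentence is general, is not tied to the chi-square test, and adds no control comparison. An unseen analysis plan could fill in detail, but the article itself already fixes the test and its groups.

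Third, the illustrated rates depend on assumed inputs and are close to nominal at a weak correlation. This is correct. They show what is possible and do not forecast this trial.

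Some stronger readings are tempting but lack support in the document:

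- A reader might infer that the high/low result reflects only who adheres. It would also carry any true shoe effect; the problem is that the two cannot be told apart.
- A reader might infer that the investigators intend to claim efficacy from this comparison. No sentence says so, and the Discussion's remark on adherent patients is used to justify patient education.
- A reader might infer that the adherence comparisons in the cited trials were equally crude. Those sources are not at hand, so this cannot be judged.

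**Conclusion.** The concern holds in limited form. The objective asks about efficacy, the outcome asks about recurrence, and the only fixed test is an unadjusted comparison of groups formed by behaviour after randomisation, with no randomised comparator. That test cannot separate a shoe effect from selection.

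With an ineffective shoe, its rejection rate runs from near nominal to over 40% across the correlations examined at standard deviation 0.7. The sizes rest on the assumed correlation or risk ratio, the assumed spread of risk and the even split; the document supplies none of these.

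The point concerns a secondary objective. The intention-to-treat log-rank and Cox analysis and the sample size are untouched.

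**What to change.** 1. Replace the crude chi-square with a high/low comparison within the footwear arm, adjusted for baseline risk factors already collected. These include the covariates that the Statistical analysis section names, with physical activity taken from the baseline questionnaire. State that the comparison is descriptive and supports no efficacy claim.
2. Align the Background and Objectives with the secondary outcome, so that all three ask about an association between adherence and recurrence.
3. If the efficacy question is kept, add as a supplementary analysis a complier average effect, with randomisation as the instrument, in all 320 patients. Fix one adherence threshold in advance and report the result beside the intention-to-treat hazard ratio. Adherence is needed only in the footwear arm, where the monitor sits, and the sample size section assumes no switching between groups.

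The cost is a little more analysis on data already planned. The complier estimate has a wider interval and assumes that allocation acts only through wearing the shoe, with no effect of wear below the threshold; if part-wear helps, it overstates the benefit. A single threshold does not show how efficacy varies with adherence, and the estimate adds no independent evidence if the intention-to-treat result is null. It should therefore stay supplementary.
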